### Study design

Given the similarities between the AFRINEST and ANISA studies, we will construct an analytical dataset which allows for pooling the data at an individual level while controlling for study and study sites. The assembly of the dataset began in October 2024, and the analysis will extend to December 2025. We will extract information from each study on baseline demographic and maternal and young infant characteristics. We will also extract temporal data on the presence of clinical signs and young infant mortality. The Strengthening the Reporting of Observational Studies in Epidemiology (STROBE) guidelines for reporting will be followed, with consideration given to Strengthening the Reporting of Observational Studies in Epidemiology for Newborn Infection (STROBE NI),^29^ as these will be observational data.

### Data analysis

#### Exposures and outcomes

We will identify baseline covariates that are common across the studies for use in adjusting regression analyses of risk for mortality and for inclusion in machine learning (ML) models. The study’s exposure is the presence of any of the seven clinical signs of PSBI. The study outcome is all-cause young infant mortality.

#### Analysis

Descriptive analyses will be performed to examine the frequency of visits where each of the signs of PSBI was found alone, as well as where signs were found in combinations. Three types of analyses of risk for mortality will be performed: case fatality, Cox regression and ML. A sensitivity analysis of mortality risk will be carried out at the study (ANISA and AFRINEST) and site levels. When infants were hospitalised, CHWs did not continue to visit the patients and document PSBI signs while the infants were in the hospital; however, CHWs did continue to assess these infants according to the standard visit schedule after discharge from the hospital, and these infants will be retained in the analysis. In ANISA, 4% of infants were hospitalised, while in AFRINEST, 5% of infants were hospitalised. Due to lack of information on the individual identification of CHW assessments, interrater reliability among CHWs cannot be determined; however, CHWs were regularly standardised for the assessment of clinical signs, as described previously.^30 31^

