Baseline data collection	CHWs collected data using standardised questionnaires during pregnancy and home visits after childbirth. The first visit was as soon as the pregnancy was confirmed, and the second was 2 months before the expected delivery date. At the first home visit after the birth of liveborn infants, CHWs/CHEWs recorded pregnancy outcomes, date of birth, place of birth, birth attendant, postpartum status of the mother, participant demographics, home environment, birth weight, postpartum neonatal characteristics at birth, history of any complaints and examination of the baby to identify any signs of illness. CHW/CHEWs recorded maternal deaths, miscarriages, stillbirths and infant deaths in the first 2 months after birth.	CHWs collected data using standardised questionnaires during pregnancy and the first home visit of liveborn infants on participant demographics, home environment, pregnancy and birth history, postpartum maternal characteristics and neonatal characteristics at birth.
Clinical sign assessment (see table 2 for definitions of signs)	CHWs in DRC and Kenya and CHEWs in Nigeria visited infants at home on days 0, 2, 6, 13, 20, 27, 34, 41, 48 and 59. They identified sick young infants with PSBI signs and referred them to registered nurses at the health centres for further assessment and management. All infants continued to be assessed for all signs of PSBI at the community level by the CHWs and CHEWs, whether or not they were enrolled in a treatment trial.	CHWs made 10 scheduled home visits over the first 60 days after birth, ideally on days 0, 2, 6, 13, 20, 27, 34, 41, 48 and 59.
Management of infants	Infants identified with >1 sign of PSBI and enrolled in antibiotic treatment trials were managed according to trial protocols.^19^,^22^	Infants were managed according to standard care at the study sites.^23 24^ Blood and respiratory cultures were obtained from infants with signs of PSBI to identify the aetiology of infections.
Mortality assessment	The study outcome was the status of the child as alive or dead (all-cause) recorded by CHWs/CHEWs during home visits to assess infants for signs of PSBI.	CHWs assessed vital status at each home visit. Death cases were referred to supervisors of the verbal autopsy study, who conducted a verbal autopsy to determine the cause of death.
Young infants enrolled (N)	84 759 infants	63 017 infants
Young infant deaths (N)	587 deaths	1635 deaths

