### Cox regression analysis

ANISA data were initially analysed using time-to-event Cox hazards regression models, as described previously.^32^ This same approach will be applied to the pooled data across the AFRINEST and ANISA studies. We will investigate the association between finding a sign of PSBI from the first visit to the end of 60 days after birth and the risk of all-cause mortality compared with not finding such a sign. Infants who were never visited or who died before a CHW visit will be left censored, and exposure periods of unknown status pertaining to the presence of signs of PSBI before the first visit will be eliminated. The period of risk for mortality will be defined as extending for 7 days after finding a sign of PSBI; a sensitivity analysis will be performed using a 14-day period of risk for mortality. We previously showed that for the ANISA data, results were similar for these two periods of risk for mortality.^32^ We will also calculate Kaplan-Meier probabilities of mortality over the young infant period. We will use Cox regression analysis to examine patterns of CHW identification of each sign as follows: a single sign found alone, the sign found with at least one other sign or any sign(s) found other than the particular sign compared with not finding any sign in association with all-cause mortality. Cox regression will also be used to examine the association between the presence of clinical signs and the occurrence of mortality during time frames of the first CHW visit to the end of day 3 (days 0 to <3), the first visit to the end of day 7 (days 0 to <7) and day 7 to the end of the 60th day (days 0 to <60). Analyses will be adjusted for covariates that are in common across all datasets.

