### Machine learning analysis

ML models will be trained to predict the risk of death for infants with signs of PSBI. The presence/absence of PSBI signs recorded over multiple visits, as well as available clinical and treatment data, will be used as input features. See supplemental table S1 (in online supplemental file 1) for a preliminary list of available predictors that are common to the ANISA and AFRINEST studies (which includes all predictors in AFRINEST) and supplemental table S2 (in online supplemental file 1) for a list of predictors available in the ANISA dataset. We will use two approaches. First, multivariate modelling will be applied to obtain precise contributions of each sign and combinations of signs to the mortality rate. In this approach, models will be built by applying standard ML models, specifically Elastic Net, XGBoost and Stabl.^33^,^35^ Presence/absence of PSBI signs at different times will be treated as separate features, and the model will predict the risk of death on a specific day given the signs on that day and in the previous 6 days.

Three models will be analysed, each specifying how the risk of death depends on PSBI signs with increasing levels of detail. We denote the predicted (dependent) variable as Y∈{0,1}

where

$$Y=\left\{ \begin{array}{l} 1,\;if\;infant\;dies\;in\;the\;7-day\;window\\ 0,\;otherwise \end{array}\right.$$

In our first (simplest) model 1, we will assume a standard logistic model for the probability of infant death given the signs in the previous 7 days.^36^ We include interaction terms between two different signs to quantify the effect of the presence of two signs on the probability of infant death. The probability that an infant dies given signs in the previous 7 days is then given by

$$\log\left(\frac{P\left(Y=1|X_{1},\ldots ,X_{p}\right)}{P\left(Y=0|X_{1},\ldots ,X_{p}\right)}\right)=\beta_{0}+\sum_{i=1}^{7}\beta_{i}X_{i}+\sum_{i=1}^{7}\sum_{j=2,\;j>i}^{7}\beta_{ij}X_{i}X_{j}+\sum_{i=8}^{p}\beta_{i}X_{i}$$

where input features $X_{i},i=1,\ldots ,7$are given by

$$X_{i}=\left\{ \begin{array}{l} 1,\;if\;sign\;i\;is\;present\;at\;any\;time\;during\;7\;days\\ 0,\;otherwise \end{array}\right.$$

and $X_{i},i=8,\ldots ,p$ are input features for each of the baseline covariates.

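### Time without an assessment is coded as absence of signs in the machine learning models and, by implication, in the Cox model after the first visit

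*Protocol article*

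**What the plan says.** **Hospital stays.** The Analysis section says that "CHWs did not continue to visit the patients and document PSBI signs while the infants were in the hospital", that visits resumed after discharge, and that "these infants will be retained in the analysis". It adds: "In ANISA, 4% of infants were hospitalised, while in AFRINEST, 5% of infants were hospitalised". It does not say how sign status is set during the stay.

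**Visit schedule.** Table 1 gives the same days for both studies, with the last visit on day 59. The earlier days are stated for ANISA as follows: "CHWs made 10 scheduled home visits over the first 60 days after birth, ideally on days 0, 2, 6, 13, 20, 27, 34, 41, 48".

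**Cox.** The Cox section says that "exposure periods of unknown status pertaining to the presence of signs of PSBI before the first visit will be eliminated". It then says: "The period of risk for mortality will be defined as extending for 7 days after finding a sign of PSBI". The reference is not finding any sign. In addition, "a sensitivity analysis will be performed using a 14-day period of risk for mortality". No rule is given for unassessed time after the first visit.

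**ML.** The Machine learning section says that "the model will predict the risk of death on a specific day given the signs on that day and in the previous 6 days". In Models 1 and 2 and in the definition printed under Model 3, a sign feature equals 1 if the sign is present in the stated period and zero in all other cases. There is no category for not assessed. The Model 3 text announces a separate feature for each day, but the definition below it switches to 1 if the sign was present on day k or any day before.

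**The concern.** Absence of a sign and absence of an assessment are different states, and mortality in the second may be higher. An infant in a long hospital stay, or one who missed a visit, has no recent CHW finding and may be sicker than an infant examined and found free of signs. If such time is placed in the no-sign group, the reference risk rises and the odds and hazard ratios move towards 1.

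That direction matters here. The Introduction says that the study looks for signs with lower mortality that might be managed without referral, and attenuation makes signs look safer. For Model 3, which is meant to capture the timing of each sign, the lag coefficients would partly describe the visit calendar.

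The plan accepts the principle elsewhere. It drops unknown status before the first visit, and it justifies the 7-day window of the case fatality analysis by the risk of misclassification when visit data are missing.

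**Working it through.** The documents give no figure of their own on this point, so there is none to reproduce.

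**1. Look-back against schedule.** Visits on days 0, 2, 6, 13, 20, 27, 34, 41, 48 and 59 give gaps of 2, 4, 7, 7, 7, 7, 7, 7 and 11 days. I counted scheduled visits in the window from day d−6 to day d.
- Days 9 to 54: exactly one visit.
- Days 55, 56, 57 and 58: none. In Model 1 an infant with a sign on day 48 is then coded free of all seven signs, unless there was an unscheduled assessment.
- One missed weekly visit empties the window for 7 days. If day 27 is missed, days 27 to 33 hold no visit.
- A hospital stay of more than 7 days has the same effect.

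**2. Model 3, read as one feature per day.** Cells per sign over days 0 to 59, without days before birth: (1+2+3+4+5+6) + 54 × 7 = 399. Cells on a scheduled visit day: 9 × 7 + 1 = 64. Cells on other days: 399 − 64 = 335, or 84%. Under the printed cumulative definition this count does not apply, because a found sign is carried forward. The two readings give different models.

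**3. Cox windows.** A sign on day 48 stops counting from day 55 or 56, depending on whether the end day is included, so 3 to 4 days before the day 59 visit are uncovered. With a 14-day window no day is uncovered. If age is the time scale (my assumption) and all infants kept to schedule, almost nobody would be exposed on those days, and those risk sets would add almost nothing to the hazard ratio. In Cox the issue therefore lies mainly with missed visits and long hospital stays.

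**4. Hospitalised infants.** 0.05 × 84,759 = 4,238 (AFRINEST) and 0.04 × 63,017 = 2,521 (ANISA), together about 6,759 of 147,776 (4.6%). Total deaths are 587 + 1,635 = 2,222. Length of stay is not given. At assumed mean stays of 3, 7 and 14 days, hospital time is 0.23%, 0.53% and 1.07% of 60-day person-time. Only the part more than 7 days after the last assessment is affected.

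**5. Direction and illustration.** Let f be the share of reference-group deaths that fall in unassessed time and p that time's share of reference person-time. As a rate-ratio approximation:

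observed HR = true HR × (1 − f) / (1 − p)

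The ratio is attenuated only if f exceeds p. With p assumed at 0.5%:

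| f (assumed) | observed HR / true HR |
|---|---|
| 5% | 0.955 |
| 10% | 0.905 |
| 20% | 0.804 |
| 30% | 0.704 |

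Neither f nor p is in the documents. The table shows direction and form, not an estimate.

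**The case against.** **The Cox part is an inference.** No sentence says that unassessed time after the first visit counts as no sign. The section follows an earlier ANISA analysis that is not shown and may contain a rule. This stands as a limit on certainty. It does not remove the point, because the article does state a rule for unknown status and confines it to the time before the first visit.

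**The exposure is detection by a CHW with a 7-day risk period.** A later death lies outside it by design. That is fair for an infant who was revisited and had no sign. It does not justify treating an infant whom nobody revisited as the same.

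**The 14-day analysis already tests this.** It does so in part: it covers infants with a sign on day 48 and deaths in days 8 to 14 after a sign. The reported similarity of the two windows is for ANISA, which supplies 1,635 of 2,222 deaths (74%), and is evidence against a large shift there. It says nothing about AFRINEST, does not help an infant who falls ill after a sign-free visit and is never reassessed, and has no counterpart in the ML.

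**Stronger readings that the documents do not support.** A reader might infer that hospital deaths of sign-positive infants generally count as sign-free. In Cox they do not: a death within 7 days of a found sign stays exposed, in hospital or not. A reader might also take the 6,759 hospitalised infants as the number misclassified. The 4% and 5% cover all admissions for any reason, and visits resumed after discharge. Finally, the 84% applies only to the one-feature-per-day reading of Model 3.

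**Conclusion.** The concern holds in a limited form. For the ML it is explicit in the formulas: not assessed is coded as absent. This affects days 55 to 58 on the ideal schedule and, beyond it, missed visits and hospital stays of more than 7 days. Model 3's text and printed definition contradict each other and must be reconciled. Under the text, 84% of its day cells per sign fall on days without a scheduled visit.

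For Cox the same treatment follows by implication for time more than 7 days after the last assessment, and the planned 14-day analysis covers it only partly.

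The expected effect is attenuation towards 1, provided that mortality in unassessed time exceeds that in assessed sign-free time. This is plausible for long hospital stays and less certain for days 55 to 58. The size cannot be derived from the documents. The point should be settled before analysis, but it does not invalidate the study.

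**What to change.** **ML.** Use the signs at the latest visit plus the number of days since that visit, and drop infant-days with no visit in the look-back. Reconcile the Model 3 text with its printed feature definition.

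**Cox.** Let each visit, positive or negative, define sign status for 7 days (14 in the sensitivity analysis). Treat later time as unknown until the next visit, either outside the risk set or as a separate not-assessed category. Removing such time may itself be informative, since missing a visit or being in hospital is related to risk, so do this at least as a sensitivity analysis next to the present rule.

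**Hospital stay.** Where both datasets hold admission and discharge dates, code the stay as its own time-varying state. The documents do not say whether these dates exist, so this part is conditional.

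**Cost.** Changes to the plan wording and to the construction of the time-dependent dataset, and the loss of some reference person-time and some late deaths. Apart from the hospital state, no new data are needed.

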##### Case fatality analysis

AFRINEST data were initially analysed using case fatality analysis, as described previously.^28^ This analysis has the advantage of simplicity of interpretation but lacks consideration of the time-varying risk of mortality. We will use data from the AFRINEST and ANISA studies for infants up to 2 months of age with at least one visit to assess the presence of clinical signs and the outcome following that visit. We will assume infants were alive for all visits until and unless a death is recorded. The case fatality rate will be calculated by sign or a combination of signs as the percentage of young infants who die within 7 days after showing that sign or a combination of signs of PSBI, divided by the total number of young infants who had shown that same sign or a combination of signs during their previous (reference) visit. We specify a 7-day window period to avoid the risk of misclassification or recall bias when no visit data were available for the extended period.

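### The case-fatality analysis counts unknown vital status as survival and does not require 7 days of follow-up after a sign, so 7-day case fatality can be understated

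*Protocol article*

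**What the plan says.** **Vital status.** The Case fatality analysis section gives one rule: "We will assume infants were alive for all visits until and unless a death is recorded".

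**Who enters.** Infants up to 2 months of age "with at least one visit to assess the presence of clinical signs and the outcome following that visit". No minimum length of follow-up is given.

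**The rate.** The numerator is "the percentage of young infants who die within 7 days after showing that sign or a combination of signs of PSBI". The denominator is all infants who "had shown that same sign or a combination of signs during their previous (reference) visit".

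**Reason for the window.** "We specify a 7-day window period to avoid the risk of misclassification or recall bias when no visit data were available for the extended period".

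**Schedule and ascertainment (Study populations, Table 1).** In AFRINEST, CHWs or CHEWs "visited infants at home on days 0, 2, 6, 13, 20, 27, 34, 41, 48 and 59". ANISA visits were "ideally on days 0, 2, 6, 13, 20, 27, 34, 41, 48 and 59". The AFRINEST outcome was alive or dead, "recorded by CHWs/CHEWs during home visits to assess infants for signs of PSBI"; ANISA also assessed vital status at each home visit. Studies were selected for recording the timing of deaths at ages 0 to <60 days, and AFRINEST recorded infant deaths over the first 2 months.

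**The concern.** A 7-day case-fatality rate needs 7 days of known vital status after each reference visit. Here death is learned of mainly through home visits, so when no later visit takes place a death may go unrecorded. The stated rule then turns missing information into survival. The infant stays in the denominator and cannot enter the numerator.

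The entry conditions do not prevent this. AFRINEST's minimum of two visits is met by days 0 and 2. ANISA needs one visit within 7 days of birth. Hospitalised infants (4% in ANISA, 5% in AFRINEST) were not visited in hospital but are retained.

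The direction matters because the Introduction says the aim is to find infants at lower risk of death who might be managed as outpatients, and to inform WHO guidance. An error that makes signs look safer works against that aim. If completeness of follow-up differs between the two studies or among their sites, the error also distorts the planned comparisons by study and site.

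**Working it through.** The document states no 7-day case-fatality rate, no loss to follow-up and no distribution of signs by visit. There is no figure to reproduce, and the unknowns below are assumed over a range.

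**1. Days observed in each window.** Observed days = min(7, 60 − visit day).
- Visits on days 0, 2, 6, 13, 20, 27, 34, 41 and 48: 7 of 7.
- Visit on day 59: 60 − 59 = 1 of 7 (2 of 7 if day 60 is counted in full).
- A full window needs a visit day no later than 60 − 7 = 53.

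So 1 of 10 scheduled visits is truncated by design. The gaps between visits are 2, 4, 7, 7, 7, 7, 7, 7 and 11 days. The window after day 48 closes on day 55, so survival through it is confirmed only if the day-59 visit takes place.

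**2. Effect of day 59, if it is kept.** Let s be the share of sign-positive reference visits at day 59 and r their 7-day risk relative to other visits. With 1 of 7 days observed and risk spread evenly over the window:

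observed/true = [(1 − s) + s·r/7] / [(1 − s) + s·r]

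| s | r | observed/true | understatement |
|---|---|---|---|
| 10% | 1 | (0.90 + 0.0143)/1.00 = 0.914 | 8.6% |
| 5% | 0.5 | (0.95 + 0.0036)/0.975 = 0.978 | 2.2% |
| 2% | 0.5 | (0.98 + 0.0014)/0.99 = 0.991 | 0.9% |
| 1% | 0.1 | (0.99 + 0.0001)/0.991 = 0.999 | 0.1% |

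The first row assumes signs and risk are equal at every visit. If day 59 is dropped, this part is zero.

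**3. Effect of loss to follow-up.** Let f be the share of windows with unknown outcome and k the relative risk of death among those lost. Counting them as alive gives:

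observed/true = (1 − f) / [(1 − f) + f·k]

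Leaving them out instead gives 1 / [(1 − f) + f·k].

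| f | k | counted alive | left out |
|---|---|---|---|
| 1% | 1 | 0.99/1.00 = 0.99 | 1.00 |
| 5% | 1 | 0.95/1.00 = 0.95 | 1.00 |
| 5% | 2 | 0.95/1.05 = 0.905 | 0.952 |
| 1% | 3 | 0.99/1.02 = 0.971 | 0.980 |
| 10% | 3 | 0.90/1.20 = 0.75 | 0.833 |

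Over these ranges loss to follow-up can do more harm than day 59. Removing the assume-alive rule clears the bias when loss is unrelated to death (k = 1) and reduces it otherwise.

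**The case against.** **Day 59 may already be out.** Nowhere does the plan say that day-59 visits serve as reference visits. It asks for the outcome following the visit and calls the reference visit the previous one, which can be read as requiring a later observation. This stands: retention is inferred from the lack of an exclusion. The phrases set no length of follow-up, however, and the sentence after the first of them supplies survival when nothing is recorded.

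**The sentence may be only a coding rule** for visit records without a vital-status entry. That reading is possible, but the text does not limit the rule to infants seen again. The stated reason for the 7-day window shows awareness of missing visits; a short window reduces the problem without removing it.

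**Larger effects are tempting to infer.** Discarding day 59 entirely would suggest a loss of 1/10 overall, or 1/7 among the seven visits from day 13 on. Crediting the observed day gives 8.6%, and 1 − (6/7 + 1/49) = 12.2%, still with equal signs and risk at every visit. The 12.2% should not be used: the case-fatality section defines no 7–59 day band, and the aim of finding lower-risk infants is not tied to one.

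**Machine learning.** A reader might carry the day-59 problem over to these models. The text says they predict death on a given day from signs on that day and the previous 6, so a sign at day 59 does not need 7 forward days. What carries over is narrower: Y is 0 for everyone not known to have died, with no rule for days after last contact.

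**Other analyses exist.** Cox regression and Kaplan-Meier curves are planned, and a condensed article may leave detail elsewhere. That would excuse silence, but here the article states the rule itself.

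**Conclusion.** The point holds in a limited form. The case-fatality section counts unknown vital status as survival and sets no completeness condition, so 7-day case fatality can be understated and cannot be overstated by this rule. That it is understated by a particular amount is not supported, because neither loss to follow-up nor the share of signs at day 59 is given. For day 59 alone, if kept, the relative understatement is about 0.1% to 8.6% (s from 1% to 10%, r from 0.1 to 1, all assumed). For loss to follow-up, observed/true is 0.99 to 0.75 (f from 1% to 10%, k from 1 to 3, all assumed). The point concerns the case-fatality analysis and, more weakly, the machine learning outcome. It does not extend to the Cox analysis, which is a time-to-event analysis.

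**What to change.** 1. Replace the assume-alive sentence. Estimate 7-day risk by Kaplan-Meier from the reference visit, with recorded deaths as events and other infants censored at the earliest of 7 days, last confirmed contact or day 60.
2. If a simple proportion is preferred, exclude every reference visit after day 53 from numerator and denominator alike, whatever the outcome, and still censor for loss to follow-up. Do not keep recorded deaths while dropping survivors who lack a later contact: that selects on outcome and pushes the rate up.
3. Report, by study, the number of reference visits with an incomplete 7-day window.
4. In the machine learning models, do not code Y = 0 for infant-days after the last confirmed contact.

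The cost is a change of wording and one dataset rule, with no new data. Denominators or time at risk shrink somewhat, and rates may rise slightly. Censoring assumes that loss is unrelated to death within the window. If those lost die 3 times as often, observed/true would still be about 0.98 to 0.83 for 1% to 10% lost, so the counts in step 3 are needed to judge what remains.
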